## Abstract

**Background:**

A high prevalence of onchocerciasis-associated epilepsy (OAE) has been observed in onchocerciasis-endemic areas with high ongoing
*Onchocerca volvulus* transmission. However, the pathogenesis of OAE remains to be elucidated. We hypothesise that the
*O. volvulus* virome could be involved in inducing epilepsy. With this study, we aim to describe the
*O. volvulus* virome and identify potential neurotropic viruses linked to OAE.

**Methods:**

In Maridi County, an onchocerciasis endemic area in South Sudan with a high prevalence of OAE, we will conduct an exploratory case-control study enrolling 40 persons aged 12 years and above with palpable onchocerciasis nodules. Cases will be participants with OAE (n=20), who will be age- and village-matched with controls without epilepsy (n=20). For each study participant, two skin snips at the iliac crest will be obtained to collect
*O. volvulus* microfilariae, and one nodulectomy will be performed to obtain adult worms. A viral metagenomic study will be conducted on microfilariae and adult worms, and the
*O. volvulus* virome of persons with and without OAE will be compared. The number, size, and localisation of onchocerciasis nodules in persons with and without OAE will be described. Moreover, the pre- and post-nodulectomy frequency of seizures in persons with OAE will be compared.

**Ethics and dissemination:**

The protocol has been approved by the Ethics Committee of the University of Antwerp and the Ministry of Health of South Sudan. Findings will be disseminated nationally and internationally via meetings and peer-reviewed publications.

**Registration:**

ClinicalTrials.gov registration NCT05868551 (
https://clinicaltrials.gov/study/NCT05868551).

**Protocol version:**

1.1, dated 09/05/2023.

## Introduction

*Onchocerca volvulus* is a filarial nematode parasite transmitted by blackflies (
*Simulium*), which causes onchocerciasis, commonly referred to as “River Blindness.” Recent epidemiological studies strongly suggest that onchocerciasis may directly or indirectly induce epilepsy, known as “Onchocerciasis-associated epilepsy” (OAE).
^
1
^
^,^
^
2
^ Onchocerciasis-associated epilepsy appears in previously healthy children between the ages of 3–18 years, with a peak onset at 8–11 years,
^
1
^ and comprises a broad spectrum of seizures, including generalised tonic-clonic, absence and nodding seizures, the latter as part of nodding syndrome.
^
3
^
^,^
^
4
^ Some OAE cases may also have stunting with delayed puberty, as part of Nakalanga syndrome.
^
1
^ Until now, diagnosing OAE has been difficult. An OAE case definition for epidemiological studies has been proposed,
^
5
^ but there is currently no test to confirm that epilepsy in a child is caused by onchocerciasis. Moreover, the fact that the pathogenesis of OAE remains unknown has kept this important public health problem from being internationally acknowledged and made it challenging to direct the necessary resources to the affected communities which are often very remotely located.
^
5
^

Multiple hypotheses concerning the pathogenesis of OAE are currently being explored.
^
6
^ It has been suggested that
*Wolbachia*, an intracellular symbiotic microorganism critical for the survival of the
*O. volvulus* parasite, could be involved, as
*Wolbachia* has been linked to the disease mechanism of onchocerciasis-related blindness.
^
7
^ However, recent studies did not detect
*Wolbachia* DNA in cerebrospinal fluid and post-mortem brain tissue of persons with OAE.
^
8
^

To our knowledge, the virome of
*O. volvulus* has never been investigated. In other parasites, a wide range of RNA viruses have been identified. For some of these parasite-hosted viruses, such as the rhabdoviruses found in
*Schistosoma solidus* and a series of nematodes, it has been suggested that they may contribute to the infection dynamics.
^
9
^
^–^
^
12
^ Rhabdoviruses are negative-sense single-stranded RNA viruses known to infect a range of different hosts, from mammals, including humans, to arthropods, plants, and parasites.
^
13
^ The fact that these viruses have such a wide range of hosts raises the question of whether these viruses are impacting multiple species by being able to infect multiple hosts naturally and/or through evolution by host jumping. We hypothesise that the
*O. volvulus* virome could be involved in the pathogenesis of OAE.

In a pilot exploratory viral metagenomic study, we performed virus-like particle (VLP) enrichment according to the NetoVIR protocol,
^
14
^ followed by Illumina deep sequencing on
*O. volvulus* adult worms obtained from persons without epilepsy in Cameroon (62 worms from nine individuals) and Ghana (46 worms from 11 individuals). Worms from different sites were collected using different protocols. During metagenomic analysis, we found that the storage of worms in RNAlater resulted in high viral read counts. Preliminary results identified a novel rhabdovirus. We are currently designing and validating a polymerase chain reaction (PCR) to be able to test serum samples of OAE patients for the presence of this virus. All other viruses were either from families not known to infect humans or sequenced in extremely low abundance.

In the current project, we propose to collect adult worms by nodulectomy and microfilariae by obtaining skin snips from persons with OAE and persons without epilepsy residing in an onchocerciasis-endemic area in South Sudan, and store them in RNAlater to optimise the yield. These will then be used for viral metagenomics analysis.

### Main study aim

To describe the
*O. volvulus* virome and to identify viruses linked to onchocerciasis morbidity, specifically OAE.

### Study objectives

This study aims to collect, in an onchocerciasis endemic area in South Sudan, good quality samples of
*O. volvulus* worms (microfilariae and adult forms). Collected samples will be analysed using viral metagenomics and investigated for the presence of the novel rhabdovirus identified in a pilot study in samples from Cameroon and Ghana.

Moreover, we will compare the number, size, and localisation of onchocerciasis nodules in persons with and without epilepsy. In addition, in the persons with epilepsy we will assess the effect of nodulectomy on the frequency of seizures.

### Hypothesis

The virome of
*O. volvulus* worms obtained from persons with OAE differs from that obtained from persons without epilepsy. A novel rhabdovirus may also be found in
*O. volvulus* samples from South Sudan.

## Methods

### Study design

An explorative case-control study.

### Study setting

South Sudan is known to have multiple endemic hotspots of onchocerciasis, including Maridi County in the Western Equatoria state (
Figure 1). Maridi County is home to over 115,000 individuals and is traversed by the Maridi River, upon which a dam was built in the 1950s.
^
15
^ The dam spillway was identified as the sole blackfly breeding site in Maridi,
^
15
^ fuelling onchocerciasis transmission in the neighbouring villages. In 2018, a high prevalence of epilepsy (4.4%) was documented in selected villages in Maridi, with a prevalence of 11.9% in Kazana-2, an area close to the Maridi Dam (
Figure 2).
^
16
^ Most (85.2%) of the persons in Maridi with epilepsy met the criteria of OAE in Maridi.
^
17
^

**Figure 1. f1:**
[figure not shown]
Location of Maridi County in Western Equatorian State, South Sudan (made in Scribble maps).

**Figure 2. f2:**
[figure not shown]
The geographical location of the eight study areas in Maridi County (adapted from Colebunders
*et al.*
^
16
^).

Annual community-directed treatment with ivermectin (CDTi) is the main method used for onchocerciasis control internationally and was introduced in Maridi in the early 2000s. However, there have been several years without treatment due to insecurity, which has allowed the disease to remain endemic in the area. The CDTi intervention was reintroduced in Maridi in 2017. Onchocerciasis transmission was assessed in December 2019 via an
*O. volvulus* antibody serosurvey (using the OV16 rapid diagnostic test) in children aged 3 to 6 years and a seroprevalence of 40.0% was found in Kazana-2 village, suggesting very high ongoing onchocerciasis transmission.
^
18
^ Moreover, blackfly biting rates of 202 flies per man per hour were observed at the Maridi Dam.
^
18
^ Annual CDTi was interrupted in 2020 because of the COVID-19 pandemic but was continued biannually (six-monthly) in 2021. Additionally, in 2019, a community-based vector control strategy known as “Slash and Clear” was implemented at the Maridi Dam. This method consists of clearing the trailing vegetation at blackfly breeding sites to reduce biting density in the nearby communities.
^
18
^

These onchocerciasis elimination measures reduced the transmission of
*O. volvulus* and OAE incidence in Maridi.
^
19
^ However, overall coverage of ivermectin of 80% is recommended to reach elimination of parasite transmission.
^
20
^ The CDTi coverage has been increasing but remains low in Maridi (only 56.6% of the population took ivermectin in 2021), and the onchocerciasis elimination goals remain far from being attained.
^
19
^

### Time schedule

The major milestones for this study will be spread over time as follows:
•Study preparation, including community sensitisation: August 2023•Recruitment, including nodulectomies: September to December 2023•Metagenomic analysis: January 2024

### Sample size calculations

Based on limited preliminary data, no sample size can be calculated. The 20 cases and 20 controls represent a convenience-based sample size and are proposed for reasons of feasibility and acceptability. The prevalence of onchocerciasis nodules in persons with and without OAE has so far not been well assessed. In a study concerning the clinical manifestations of epilepsy in Maridi, onchocerciasis nodules were only reported in 5.8% of persons with nodding syndrome and in 0.7% of persons with epilepsy without nodding syndrome.
^
21
^

### Study population and samples to be collected

Twenty OAE cases (≥12 years old) with at least one onchocerciasis nodule and 20 age- and village-matched non-epileptic controls with at least one onchocerciasis nodule will be recruited into the study. A person will be considered having OAE if he/she matches the criteria of the most recent case definition of OAE.
^
5
^

### Study procedures

Selection and enrolment of the study participants

After obtaining informed consent, persons with epilepsy attending the epilepsy clinic at Maridi Hospital, at least 12 years old and living in Kazana-1 or Kazana-2 villages, will be carefully examined for the presence of onchocerciasis nodules by trained personnel. The main parts of the body that will be examined are the head, neck, chest, arms, lumbar region, buttocks, thighs, and legs. Persons with epilepsy will also be interviewed to assess whether they meet the criteria of OAE.
^
5
^ If they meet these criteria, they will be asked to participate in the study. Recruitment of OAE cases will be consecutive.

After all persons with OAE have been selected for the study, controls will be identified during a house-to-house survey in Kazana-1 and Kazana-2. All persons without epilepsy between the ages of 12 and 30 years will be examined for the presence of onchocerciasis nodules. For each case with OAE, a control with at least one onchocerciasis nodule with a similar age (±3 years), sex and ivermectin use will be asked to participate in the study. Both OAE cases and controls will only be enrolled after written informed consent is obtained, as well as assent from the children 12–17 years old.

Interview and examination

For each study participant, pre-tested questionnaires
^
22
^ will be completed. This questionnaire will include questions about potential onchocerciasis-related symptoms (epilepsy, cognitive decline, skin, and eye problems) and past ivermectin use. All participants will be examined, and the number, size, and localisation of the nodules will be noted. Moreover, in follow-up questionnaires,
^
23
^ we will record the status of the wound and the number of seizures since the nodulectomy 10 days and one-month post-nodulectomy.

*O. volvulus* antibody testing

Blood will be obtained by finger prick for Ov16 rapid diagnostic testing. Moreover, four dry blood spots on filter paper and 5 mL of venous blood will be collected per person to allow for the possibility of using these samples for future pathogenesis and
*O. volvulus* diagnostic studies.

Nodulectomy

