*O. volvulus* worms in RNAlater will be preserved initially at the Maridi hospital in a -20°C freezer. Later samples will be transferred under cold chain conditions, first to a -80°C freezer at the Public Health Laboratory of the Ministry of Health of South Sudan in Juba and later to a -80°C freezer at the Rega Institute at the KU Leuven in Belgium.

Viral metagenomic analysis

All collected worms will be sent to the Rega Institute under the Nagoya agreement. Worms will be processed following the NetoVIR protocol adapted for adequate homogenization.
^
14
^ In short, worms will be diluted in 500μl PBS and homogenized in a Precellys® Evolution tissue homogenizer (Bertin Technologies) with 2.8 mm zirconium oxide beads (Precellys) at 4500 rpm for 1 min. For each processed batch of worms, a negative control consisting of only PBS will be taken along. Next, the samples will be centrifuged at 17,000 g for 3 min and 150 μl supernatant of each sample will be subsequently filtered through a 0.8 μm filter (Sartorius). This filtrate will be treated with a mix of Benzonase (50 U, Novagen) and Micrococcal nuclease (2000 U, New England Biolabs) to digest remaining free-floating eukaryotic and bacterial nucleic acids. Viral DNA and RNA will be then extracted using the Kingfisher Flex system (Thermofischer), Applied Biosystems in combination with the MagMAX™ Viral/Pathogen Nucleic Acid Isolation Kit (Thermofischer). DNA and RNA will be amplified using the Complete Whole Transcriptome Amplification kit (WTA2, Merck), and resulting PCR products will be further purified and prepared for sequencing with the Nextera XT kit (Illumina). The final sequencing libraries will be cleaned up with Agencourt AMPure XP beads (Beckman Coulter, Inc.) using a 0.6X ratio of beads to sample. Finally, paired-end sequencing will be performed on the Nextseq 550 platform (Illumina) for 300 cycles (2x150bp) with an estimated 10 million reads per sample. All resulting sequences will be run through the ViPER pipeline (
https://github.com/Matthijnssenslab/ViPER) on the infrastructure of the Vlaamse (Flemish) Supercomputer Center® (VSC) to evaluate the read quality, perform

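### Seeking controls only after all cases are selected ties case status to collection date, and probably to field handling and storage time, in the main virome comparison

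*Protocol article*

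**What the plan says.** Under Study procedures, cases come from the epilepsy clinic: "Recruitment of OAE cases will be consecutive". The control survey follows: "After all persons with OAE have been selected for the study, controls will be identified during a house-to-house survey in Kazana-1 and Kazana-2". It examines everyone without epilepsy aged 12 to 30 in the two villages, and the matching rule reads "For each case with OAE, a control with at least one onchocerciasis nodule with a similar age (±3 years), sex and ivermectin use". The section on study population adds village. Collection date is not a matching variable in either place.

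The Time schedule gives one window for both groups, "Recruitment, including nodulectomies: September to December 2023", followed by "Metagenomic analysis: January 2024".

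Nodules are digested in collagenase with hourly checks, teased apart by hand, washed three times in Percoll and placed in RNAlater. They are then frozen at -20°C in Maridi, and later moved to -80°C in Juba and afterwards in Belgium. No shipment dates are given. At the homogenisation step in Belgium, "For each processed batch of worms, a negative control consisting of only PBS will be taken along". The article does not say how cases and controls are spread over batches.

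**The concern.** The main hypothesis is that worms from persons with OAE carry a different virome from worms of persons without epilepsy. Anything technical that tracks case status can imitate such a difference or hide one. Read as written, the recruitment rule puts case collection mostly early and control collection mostly late. Growing skill in digestion and washing, any change of reagent lot, and time in the freezer would then all tend to differ by group.

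The Percoll wash matters most, because the article relies on it to remove most human viral contaminants. A drift in technique could change which viruses are seen. The pilot also found that storage medium affected viral read counts. That is evidence on medium, not on duration, but it shows that yield depends on handling before the laboratory.

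The Discussion proposes PCR screening of young children if candidate viruses are found, so a spurious signal would misdirect later work.

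**Working it through.** **Inputs from the article.** There are 20 cases and 20 controls ("The 20 cases and 20 controls represent a convenience-based sample size"), controls are sought after cases, collection runs September to December 2023, and analysis is in January 2024. The article gives no power calculation to reproduce ("Based on limited preliminary data, no sample size can be calculated") and states no alpha. The two-sided 0.05 level used below is an assumption.

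**1. Gap in collection date.** The window is 30 + 31 + 30 + 31 = 122 days. If cases fill the first half evenly and controls the second (assumed), the mean dates are day 30.5 and day 91.5. The mean gap is 91.5 − 30.5 = 61 days. A single pair could differ by up to 122 days. Since analysis is one later stage, storage time would differ by a similar amount.

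**2. What an aligned artefact does.** Suppose a virus has detection probability p in both groups, with no true association. Handling or storage raises detection by d in one group only. The table gives the exact probability that Fisher's test (20 versus 20) is significant:

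| Baseline p | d = 0 | 0.10 | 0.20 | 0.30 | 0.40 |
|---|---|---|---|---|---|
| 0.10 | 1.2% | 7.2% | 24% | 49% | 74% |
| 0.30 | 2.5% | 5.9% | 16% | 35% | 60% |

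The values of p and d are assumptions; the article gives neither.

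**3. Partial alignment.** Take two equal collection periods of 20 samples, with a share s of the cases in the first. Expected detection is p + s·d in cases and p + (1 − s)·d in controls. The spurious difference is therefore (2s − 1)·d. The variance inflation from adjusting for period is 1/(1 − (2s − 1)²).

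| s | Spurious difference at d = 0.30 | Variance inflation |
|---|---|---|
| 1.0 | 0.30 | not separable |
| 0.9 | 0.24 | 2.78 |
| 0.75 | 0.15 | 1.33 |
| 0.5 | 0 | 1.00 |

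Only complete alignment makes adjustment impossible. Below that, adjustment is possible if dates are recorded, at a cost in precision. The same formula applies to laboratory batches: keeping pairs together gives s = 0.5 and removes the batch component. It does not remove the collection-time component.

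**4. Reach of the blank.** The PBS control is described at homogenisation. It has not been through collagenase, Percoll, RNAlater or the saline used for skin snips. It can help to reveal reagent contamination from homogenisation onward, but nothing introduced earlier.

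**The case against.** A reader might infer that case status coincides with laboratory batch, so that, for example, one contaminated batch of 10 made up only of cases would give 10/20 against 0/20 (Fisher p = 0.00044). The documents do not support this. Analysis is scheduled after recruitment ends, all worms go to one laboratory, and nothing says they are run in order of arrival. If 40 samples were put at random into two batches of 20, status and batch would coincide completely with probability 2/C(40,20), about 1.5 × 10⁻¹¹. A journal article may also leave batch layout and laboratory masking to the full protocol or a laboratory procedure. In addition, contamination of a whole batch is what the PBS blank helps to find. This objection stands: the batch point is a risk to guard against, not a stated flaw.

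Three further points limit the concern.
- The article orders selection and identification, not surgery, so collection dates may overlap.
- One trained doctor performs the nodulectomies, no change of reagent lot is described, and matching on ivermectin use partly covers treatment timing.
- No effect of storage duration is shown, and the study is explicitly exploratory.

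These points make the alignment incomplete and its effect unknown. They do not remove it. The order of recruitment is a stated rule, date is not matched, and the field steps precede the only negative control described.

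**Conclusion.** The point holds in limited form. Sequential recruitment aligns case status with collection date and probably with field handling and storage time. The one blank described cannot detect artefacts from the field stage.

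The degree of alignment is unknown: about 61 days on average under an even split, and less if nodulectomies overlap. The false-positive rates rest on assumed artefact sizes and full alignment. They show how sensitive a comparison of 20 with 20 is, not what will happen. It would be wrong to say that no later analysis could separate a technical difference from an OAE difference, since that is true only if alignment is complete. The change is worth making because it protects the main comparison at little cost.

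**What to change.** 1. Run the house-to-house survey alongside case recruitment. It examines everyone without epilepsy aged 12 to 30 in both villages in any case, so a list of nodule-positive persons can be built before the cases are complete. Draw each matched control from that list so that its collection falls close in time to that of its case.
2. Process both members of a pair in the same extraction, amplification, library and sequencing batch, in random order, under codes that hide case status. The January 2024 start allows this. It does not replace step 1, because it leaves the collection-time component in place.
3. Record collection and storage dates for every sample, and check the case-control comparison against them.

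The cost is that clinic recruitment and the survey overlap in time, which is some added field coordination, and that a batch-allocation list with coded labels is needed. No participants or procedures are added.

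### Cases have no upper age limit, but controls are sought only at 12 to 30 years and within ±3 years, so a case aged 34 or older has no admissible control

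*Protocol article*

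**What the plan says.** **Age of cases.** Three places in the protocol article give a lower limit and no upper one.
- The Methods part of the Abstract speaks of "enrolling 40 persons aged 12 years and above with palpable onchocerciasis nodules", which covers both groups.
- Study population and samples to be collected has "Twenty OAE cases (≥12 years old) with at least one onchocerciasis nodule".
- Study procedures, under selection and enrolment, describes clinic attenders who are "at least 12 years old and living in Kazana-1 or Kazana-2 villages".

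Sampling is not selective by age: "Recruitment of OAE cases will be consecutive".

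**Controls.** The same enrolment text fixes three things.
- Order: "After all persons with OAE have been selected for the study, controls will be identified during a house-to-house survey".
- Age range searched: "All persons without epilepsy between the ages of 12 and 30 years will be examined for the presence of onchocerciasis nodules".
- Matching rule for each case: "a control with at least one onchocerciasis nodule with a similar age (±3 years), sex and ivermectin use will be asked to participate".

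**Size.** Sample size calculations says "The 20 cases and 20 controls represent a convenience-based sample size", one control per case.

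**The concern.** The case criterion, the age range of the control survey and the matching tolerance are all stated, and they do not fit together. The case range is open at the top, while the range from which controls are drawn closes at 30. The only other age range given for OAE, 3 to 18 years in the Introduction, is age at onset and does not limit the current age of a clinic patient.

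Cases come consecutively from an epilepsy clinic, so they are prevalent patients of whatever age attends. Study setting dates the dam to the 1950s and names its spillway as the only blackfly breeding site identified in Maridi. Older patients are therefore conceivable, although the article does not say how many there are.

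If such a case is enrolled, the team must either leave the case without a control or depart from the age rule. With a survey that stops at 30, a departure can only produce a control who is too young. Age is one of the factors the authors chose to match on, and older people have had longer to accumulate exposure. Younger controls could therefore distort the comparison of nodule number and size, and the virome comparison would no longer be fully age-matched.

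**Working it through.** The plan states no figure of its own on this point, so there is nothing to reproduce. The check is whether a case's matching window overlaps the survey's age range.

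**Inputs (all from the protocol article)**
- Case age a: 12 or more, no maximum (Abstract; Study population; Study procedures).
- Control survey: 12 to 30 years (Study procedures).
- Tolerance: ±3 years (Study procedures).
- 20 cases and 20 controls (Sample size calculations).

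**Step 1: admissible control ages.** For a case aged a, in completed years, these are the ages that lie both in [a − 3, a + 3] and in [12, 30].

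| Case age | Window | Admissible control ages | Number of ages |
|---|---|---|---|
| 27 | 24–30 | 24–30 | 7 (full) |
| 28 | 25–31 | 25–30 | 6 |
| 29 | 26–32 | 26–30 | 5 |
| 30 | 27–33 | 27–30 | 4 |
| 31 | 28–34 | 28–30 | 3, all younger |
| 32 | 29–35 | 29–30 | 2, all younger |
| 33 | 30–36 | 30 | 1, younger |
| 34 | 31–37 | none | 0 |

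The overlap is empty once a − 3 > 30, that is from a = 34 upwards. If the stated range is read as excluding age 30 itself, the first age without a control is 33. At the lower end no problem arises, because both groups start at 12: a case aged 12 still has controls aged 12 to 15.

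**Step 2: size of a forced departure.** If a control is nevertheless taken from the survey, the age gap is at least a − 30 years: 4 years for a case of 34, 10 years for a case of 40.

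**Step 3: how many cases could be affected.** The article does not give the share p of eligible cases aged 34 or older, so the range below is assumed. The expected number without a control is 20p. The probability of at least one is 1 − (1 − p)^20, treating cases as independent.

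| Assumed p | Expected of 20 | Probability of at least one |
|---|---|---|
| 0% | 0 | 0 |
| 5% | 1 | 0.64 |
| 10% | 2 | 0.88 |
| 20% | 4 | 0.99 |
| 30% | 6 | above 0.99 |

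These counts reflect age alone. A control must also carry a nodule and be similar in sex and ivermectin use, which narrows the pool further near the upper limit.

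**The case against.** The strongest reply is that nothing shows the problem will occur. The article gives no age distribution for OAE patients, clinic attenders or nodule carriers. If all 20 enrolled cases are 33 or younger, every one has at least one admissible control age. This stands: the conflict between the rules is certain, but its practical effect is not.

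A second reply is that little is lost. The study is exploratory with a convenience sample, and the data analysis plan states no pair-wise analysis. A case without a control still contributes to the virome description, the nodule description and the seizure comparison before and after nodulectomy, which uses cases only. This also stands. What is at risk is a matched control and the age balance of the comparison, not the case's data.

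A third reply is that the full protocol may hold a rule for unmatched cases. It may, but such a rule would not make the stated age ranges agree.

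Two stronger readings are tempting, and the documents do not support them.
- A reader might infer that cases would already have had nodulectomy before the mismatch came to light. The enrolment text fixes only the order of selection, and Time schedule places recruitment and nodulectomies in one period, September to December 2023.
- A reader might infer that older hosts carry older worms, so that younger controls confound the virome through worm age. The Discussion puts adult worm life at up to 10 years, and nothing in the article links worm age to host age among adults.

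**Conclusion.** The point holds as an internal conflict between stated rules. Under the article's own criteria a case aged 34 or older cannot be given a control, and cases aged 31 to 33 can be matched only to younger people. The threshold follows from 30 + 3 = 33 and needs no assumption beyond ages in completed years and a survey that includes age 30.

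The size is unknown. It may be zero, and would be about 1 to 6 of 20 cases if 5% to 30% were 34 or older, a range that is purely illustrative. The consequence is limited to possible bias in the nodule comparison and a weaker age-matched virome comparison. For cases aged 31 to 33 the age gap stays within the 3 years that the protocol accepts for everyone; the issue there is only that it always runs in one direction. Because the remedy is simple and protects the planned 20:20 matched design, the change is worth making.

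**What to change.** In the enrolment text of Study procedures, replace the fixed upper limit of 30 years for the control survey with the age of the oldest enrolled case plus 3 years, keeping the lower limit of 12. The survey follows case selection, so that age is known when the survey starts. Every case then has a full window on the upper side, no case age is left without admissible control ages, and 20:20 is unchanged. The cost is one sentence and the palpation of some additional older residents in households that are visited anyway.

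Capping the age of cases would also align the ranges but is less attractive. A cap of 33 leaves every case at least one admissible control age, but a full ±3-year window on the upper side needs a cap of 27 (27 + 3 = 30). Either cap could turn away nodule-positive cases, who may be scarce: Sample size calculations cites nodules in 5.8% of persons with nodding syndrome and 0.7% of persons with other epilepsy in Maridi.

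### The control-selection rule does not name village, so it does not deliver the age and village matching stated in the Abstract and the study population section

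*Protocol article*

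**What the plan says.** The Abstract (Methods) states: "Cases will be participants with OAE (n=20), who will be age- and village-matched with controls without epilepsy (n=20". The section Study population and samples to be collected gives the same two factors: "20 age- and village-matched non-epileptic controls with at least one onchocerciasis nodule will be recruited into the study".

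Study procedures, under Selection and enrolment of the study participants, gives a different list. The selection is made case by case, "For each case with OAE, a control with at least one onchocerciasis nodule", and the person chosen must be one "with a similar age (±3 years), sex and ivermectin use will be asked to participate in the study". Village is not among these factors. It enters this section only as the recruitment area. Cases are to be "at least 12 years old and living in Kazana-1 or Kazana-2 villages", and "controls will be identified during a house-to-house survey in Kazana-1 and Kazana-2".

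**The concern.** The matching rule decides who is approached as a control and who then has a nodulectomy. It also decides which differences between the groups the design removes. A field team following the enrolment text would match on sex and ivermectin use, which the other two statements do not mention, and would have no instruction to match on village, which both of those statements promise.

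The main hypothesis is that the worm virome differs between persons with and without OAE, and the data analysis plan compares the two groups. If worms from the two villages carry different viruses, and the groups differ in village mix, the comparison is confounded by village. The recruitment routes give no assurance of equal mixes: cases come consecutively from a hospital clinic, controls from a house-to-house survey.

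**Working it through.** **Step 1. The three statements side by side.**

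| Place | Age | Village | Sex | Ivermectin use |
|---|---|---|---|---|
| Abstract, Methods | yes | yes | no | no |
| Study population and samples to be collected | yes | yes | no | no |
| Study procedures, Selection and enrolment | yes, ±3 years | not named | yes | yes |

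Only age is common. The enrolment text is not simply a more detailed version of the shorter rule: it adds two factors and leaves one out.

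**Step 2. Does the restriction to two villages amount to village matching?** Selection is one control per case. Under the enrolment text, a Kazana-1 case with a Kazana-2 control of similar age, the same sex and similar ivermectin use is a valid pair. Under the other two statements it is not. Restriction keeps out persons from other villages, but it does not make the shares of Kazana-1 and Kazana-2 equal in the two groups.

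**Step 3. How large could the effect be?** The document gives no figure from which this can be calculated, so all inputs here are assumed. Take a virus unrelated to OAE, carried by the worms of a proportion a of people in Kazana-2 and b in Kazana-1. Let f be the share of a group that lives in Kazana-2.

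- Detection in a group = f × a + (1 − f) × b
- Odds ratio (OR) = odds of detection in cases ÷ odds of detection in controls

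| a / b | f, cases / controls | Detection, cases | Detection, controls | OR |
|---|---|---|---|---|
| 60% / 40% | 80% / 70% | 0.8×0.6 + 0.2×0.4 = 0.56 | 0.7×0.6 + 0.3×0.4 = 0.54 | 1.08 |
| 60% / 40% | 80% / 50% | 0.56 | 0.5×0.6 + 0.5×0.4 = 0.50 | 1.27 |
| 80% / 20% | 80% / 70% | 0.8×0.8 + 0.2×0.2 = 0.68 | 0.7×0.8 + 0.3×0.2 = 0.62 | 1.30 |
| 80% / 20% | 80% / 50% | 0.68 | 0.5×0.8 + 0.5×0.2 = 0.50 | 2.13 |
| 80% / 20% | 100% / 50% | 0.80 | 0.50 | 4.00 |

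For example, in the fourth row, (0.68/0.32) ÷ (0.50/0.50) = 2.13. With f equal in both groups, as matching on village within pairs ensures, detection is the same and the OR is 1. If the village shares of cases and controls are exchanged, each OR becomes its reciprocal (2.13 becomes 0.47), so the direction is open as well.

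**The case against.** The lists can be read as complementary. Nothing says that village is not matched, and one rule with all four factors would satisfy all three statements. This is also a journal article, and the full protocol may carry the complete rule. That reading is possible and shows how easy the repair is. It does not remove the conflict: two places in the article promise village matching, and the place that describes the selection leaves it out. Brevity could explain a short list in the Abstract, but the study population section is part of the Methods and gives the same short list.

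Several stronger readings are tempting and are not supported.

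- **Cases will come mostly from Kazana-2.** Study setting reports an epilepsy prevalence of 11.9% in Kazana-2 against 4.4% over the selected villages, but it gives no prevalence or population for Kazana-1. The split of cases between the two villages cannot be inferred. Controls must also carry a nodule, so if transmission is higher in Kazana-2, eligible controls may concentrate there too.
- **The bias is large.** The 80%/20% carriage contrast is an assumed extreme. Study setting names a single blackfly breeding site, which speaks against sharply different worm populations in neighbouring villages. With milder inputs in one or both respects, the OR is about 1.1 to 1.3.
- **The planned analysis is invalidated.** The article says only that viromes will be compared. It describes no matched-pair analysis that could fail.

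It is also fair that the study is exploratory, with a convenience sample of 20 per group, and that describing the virome does not depend on the matching.

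**Conclusion.** The inconsistency stands on the wording alone and needs no assumption. As written, the enrolment rule does not deliver the village matching claimed elsewhere, and the Abstract and study population section leave out two factors on which controls will be selected. The consequence is possible confounding of the virome comparison by village. It arises only if virus carriage differs between the villages and the village mix differs between the groups, and the document shows neither. The range of about 1.1 to 4 for the spurious OR illustrates assumed inputs and is not an estimate. The point is worth correcting before enrolment because the rule fixes who is enrolled, and with 20 cases and 20 controls later adjustment has little information to work with.

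**What to change.** Before enrolment, put one rule in the Abstract, in Study population and samples to be collected, and in Selection and enrolment of the study participants: each control is matched to its case on village (Kazana-1 or Kazana-2), age ±3 years, sex and ivermectin use. Record village and a pair identifier for every participant. If no full match can be found for a case, adjust for the unmatched factor in the comparison. The document gives no ground for ranking village above ivermectin use or the reverse, so the order in which factors may be relaxed is for the investigators to set.

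The cost is wording in three places and two recorded items. The downside is that a tighter match may be harder to fill. Sample size calculations cites nodules in only 5.8% of persons with nodding syndrome and 0.7% of those with other epilepsy in Maridi, and gives no figure for persons without epilepsy, so how many eligible controls exist is unknown.
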